## Abstract

**Introduction:**

Dementia risk reduction through lifestyle modification has much potential but is not yet implemented in routine clinical care. Currently, there are no preventive interventions available for memory clinic patients. Therefore, the aim of The Lifestyle Intervention in the memory clinics of General and academic Hospitals Trial (LIGHT) is to examine the (cost)effectiveness of a multidomain intervention combining lifestyle coaching with risk self-management for patients with subjective cognitive decline (SCD) and mild cognitive impairment (MCI).

**Methods:**

LIGHT is a 1-year multi-center randomized controlled trial for dementia risk reduction by improving brain health through lifestyle modifications in memory clinic patients without dementia. Starting early 2025, the trial aims to include 300 older adults (≥ 50 years) with SCD or MCI, with presence of ≥ 2 modifiable dementia risk factors, recruited via the memory clinics of Dutch hospitals. Participants are randomized 1:1 to either the intervention group or control group. The intervention consists of three components: (1) three individual sessions with a certified lifestyle coach to set and work on personal goals, (2) vouchers for access to brain-healthy services from local providers, and (3) access to an online self-management platform (www.breinzorg.nl) providing psychoeducation on dementia risk reduction through lifestyle. The control group receives general health advice. The primary outcome is 1-year change in modifiable dementia risk captured by the LIfestyle for BRAin Health 2 (LIBRA2) index consisting of coronary heart disease, diabetes, hypercholesterolemia, hypertension, depression, obesity, smoking, high physical activity, and chronic kidney disease, high alcohol intake, high cognitive activity, healthy diet, hearing impairment, sleep disturbances, and social participation. Secondary outcomes include cognitive functioning, health-related quality of life, activities of daily living, self-efficacy, care use, as well as change in individual risk factors.

**Conclusion:**

LIGHT will provide insight into the implementation and (cost-)effectiveness of a lifestyle intervention for indicated prevention in a memory clinic setting.

**Trial registration:**

Clinicaltrials.gov: NCT06832761 (date 2025-02-18), OMON: 57,198.

**Supplementary Information:**

The online version contains supplementary material available at 10.1186/s13195-025-01947-9.

## Background

Dementia is a major public health challenge according to the World Health Organisation [1]. Currently, over 57 million people live with dementia worldwide, increasing to over 150 million cases in 2050 [2]. Over the past decade, increasing evidence suggests that universal (targeting entire populations) or selective (targeting specific groups within populations) prevention of dementia through lifestyle modifications could have large impact [3]. Dementia has a multifactorial aetiology, for which modifiable risk factors jointly account for about 45% of dementia cases worldwide [3, 4]. Most of these factors relate to cardiometabolic health, such as hypertension, hypercholesterolemia, obesity, diabetes, low physical activity, and smoking, but other lifestyle factors such as depression, poor sleep, lack of social contacts, or low cognitive activity also contribute.

Occurrence of risk factors vary widely across individuals, and effective risk reduction requires personalized and multidomain lifestyle interventions [5, 6]. Some previous lifestyle intervention studies found improvement or reduced decline in cognition following the intervention [7–9], but most studies generally did not find an effect of multidomain lifestyle interventions on cognitive outcomes [6, 10–12]. This might be due to problems with adherence to the intervention and relatively short follow-up periods [13]. However, when considering brain health or dementia risk scores such as LIfestyle for BRAin Health (LIBRA), ANU Alzheimer’s Disease Risk Index (ANU-ADRI), or Cardiovascular Risk Factors, Aging, and Incidence of Dementia (CAIDE), studies consistently show decreased dementia risk scores across the multidomain lifestyle intervention groups [7, 11, 14–16]. These results are promising and suggest that implementing multidomain lifestyle interventions may help change people’s behavior towards a healthier lifestyle to effectively reduce dementia risk.

So far, most research comes from studies in the general population, while evidence for indicated prevention in memory clinics (in stages of subjective cognitive decline (SCD) and mild cognitive impairment (MCI)), is lagging behind. These patients generally have worse health and lifestyle profiles and are at higher risk for dementia [17, 18]. While they might, thus, benefit from preventive measures, there are currently no integrated preventive measures for dementia risk reduction in routine clinical care [19]. Real-world implementation of interventions studied in earlier WW-FINGER trials is difficult due to strict programs and high intensity [20]. Therefore, it is necessary to explore more personalised intervention options and to assess their implementability in healthcare.

Therefore, the primary objectives of the Lifestyle Intervention at General and academic Hospitals Trial (LIGHT) are to: (1) test the effectiveness of a lifestyle intervention on improving the dementia risk profile of people with SCD and MCI in a randomized controlled trial (RCT), as compared to general health advice (2) identify barriers, facilitators and evaluate strategies for sustainable implementation of the lifestyle intervention, and (3) estimate the cost-effectiveness of the lifestyle intervention from a lifetime horizon and societal perspective.

## Methods

### Study design

LIGHT is a multi-center RCT assessing the (cost-)effectiveness of a 1-year personalized lifestyle intervention as compared to usual healthcare and general health advice with 300 participants. Participating research centers include Maastricht University and Amsterdam University Medical Center. Outcome measurements are conducted at baseline and at the end of the 1-year intervention. LIGHT has been approved by the medical ethical committee of MUMC+ (NL86513.068.24) and is registered at Dutch trial register OMON (NL-OMON57198) and ClinicalTrials.gov (NCT06832761, registration date February 18th 2025). This study will be conducted in accordance with the ethical conduct and juridical laws of the Declaration of Helsinki (2013), Good Clinical Practice (GCP) as defined by the International Conference on Harmonization (ICH) Guidelines, and the Medical Research Involving Human Subjects Act (WMO). Results will be reported in line with the Consolidated Standards Of Reporting Trials (CONSORT) guidelines [21].

### Inclusion criteria

Inclusion criteria are: 1) ≥ 50 years of age at pre-screening; 2) memory clinic patients with clinician-confirmed SCD or MCI; 3) Presence of ≥ 2 modifiable risk factors for dementia specified by the updated LIBRA2 score [22, 23]. Persons were classified as SCD when being referred to the memory clinic with subjective cognitive complaints but without showing objective cognitive impairments on neuropsychological assessment [24]. A diagnosis of MCI was defined by impairment (<−1.5 SD below normative mean) on at least one cognitive domain measured by neuropsychological assessment [25]. Only risk factors that are potentially modifiable within one year are considered f or inclusion (i.e., hypercholesterolemia, hypertension, depressive mood, obesity or overweight, current smoking, low physical activity, high alcohol consumption, low cognitive activity, unhealthy diet, poor sleep quality, low social participation).

### Exclusion criteria

Exclusion criteria are: (1) having a clinician-confirmed diagnosis of dementia as defined by the DSM-V criteria; (2) insufficient understanding of the Dutch language; (3) conditions affecting safe and continuous engagement in the intervention (e.g. under treatment for current malignant diseases, major psychiatric disorders (e.g. major depression, psychosis, bipolar disorder), other conditions preventing co-operation as judged by the local study nurse or consulted physician at the local study site; (4) participation in any other research intervention trial at time of pre-screening and throughout the study period.

### Recruitment and pre-screening

Recruitment takes place in memory clinics of academic (Maastricht University Medical Center + and Amsterdam University Medical Center) and general hospitals in the Netherlands. Patients are actively recruited by physicians and psychologists at the participating memory clinics through explanation, flyers, posters, etc. Both memory clinics of the participating centers have an established research infrastructure, increasing feasibility of recruitment. Other recruitment routes involve large ongoing cohort studies at the memory clinics. Potentially eligible participants first receive detailed oral explanation by the researchers, and, if interested, this is followed up by written information about the study. After receiving the information, participants will have at least 7 days before deciding on participation. The researcher then performs a pre-screening to check eligibility based on the inclusion criteria through a short telephone questionnaire. Eligible participants are invited for the baseline visit, where written informed consent is signed.

### Randomization and blinding

After the baseline visit, participants are randomized with a 1:1 ratio to either the intervention group or control group. Block randomization (in variable groups of two and four) stratified for study centre and diagnosis (SCD or MCI) is used. Randomization is done by a computer-generated allocation scheme integrated in the Castor electronic data capturing system (Castor EDC, Amsterdam, The Netherlands). Researchers executing cognitive assessments at follow-up are blinded for group allocation. Group allocation is not actively disclosed to participants, but complete blinding is unlikely due to the nature of the intervention.

### Personalized lifestyle intervention

An overview of the study design is shown in Fig. 1. The personalized lifestyle intervention includes three components:

Lifestyle coach

The first and main component of the intervention involves three personal sessions with a certified lifestyle coach. At the start of the intervention (2–4 weeks after the baseline assessment), the coach will provide tailored advice (on site or through an online video call). The coach discusses the individual lifestyle risk profile (based on baseline LIBRA2 measures, see below) and through motivational interviewing [26], suggests lifestyle changes based on the risk factors with suggested room for improvement. The participant and lifestyle coach agree on an individual plan and set realistic personal goals, also considering the personal aims and wishes of the participant. Tailored advice may for example comprise specific advice on how to be more physically active or to adopt more healthy dietary choices based on the participants’ personal preference and motivation. Participants may be referred to suitable professional help (e.g. dietician, stop smoking program) or community-based lifestyle initiatives (e.g. free sports initiatives for elderly, cooking groups) to facilitate and maintain behavioural change. Two follow-up sessions 3 and 9 months after the first visit are intended to discuss progress and, if needed, adjust or set new personal goals. Sessions will take 1 to 1.5 h.

2.Voucher program

The second component is a voucher program, which was co-developed with regional partners, to support participants in making a first step towards a brain-healthy lifestyle. The voucher program is inspired by a similar program that is implemented in the Programme Dementia Prevention (pdp) in Luxembourg [27]. Participants receive up to two vouchers from the lifestyle coach per visit (with a total of six vouchers, each worth 50 euros) to support brain healthy behaviours tailored to the individual risk profile and goals as discussed with the lifestyle coach. These vouchers provide access to services across multiple domains: physical activity, social participation, cognitive activity, and healthy diet and include, among others, gym memberships, free entrance to museums, or fresh vegetable and fruit from local farmers. The lifestyle coach has an advisory and motivational role in the voucher usage.

3.Access to online platform

Finally, participants receive access to the online risk self-management platform BreinZorg (‘BrainCare”, www.breinzorg.nl). The platform was developed through co-creation with the target group and provides psychoeducation, tips, and exercises to maintain brain health, with learning modules for each LIBRA2 factor. Participants will also receive a binder with general information about the LIBRA2 factors in relation to brain health and dementia. It additionally includes the participants’ personal risk profile, personal goals and evaluation, and instructions for the usage of the vouchers and BreinZorg.

**Fig. 1 Fig1:**
[figure not shown]
LIGHT study design

### Control group

The control group receives general health advice through a similar binder, including the same general information about the LIBRA2 factors in relation to brain health and dementia. Participants in both groups will receive regular online newsletters and updates as well as gift vouchers (75 euros in total) for their participation.

### Baseline and outcome measurement

All study participants undergo a baseline measurement and one follow-up outcome measurement at 12 months at the research site. Measurements include an assessment of demographics, medical history and medication, cognitive testing, clinical measures, blood sampling and questionnaires. In total, research visits take up to 1.5 h. Table 1 gives an overview of all primary and secondary outcomes.

**Table 1 Tab1:** LIGHT data collection

Measures	Type of outcome
**Lifestyle score**	
LIfestyle for BRAin Health 2 (LIBRA2)	Primary
**Cognition**	
15-Word Verbal Learning Test	Secondary
Digit Symbol Substitution Test 90 s	Secondary
Wechsler Adult Intelligent Scale (WAIS) digit span	Secondary
Trail Making Test (TMT)	Secondary
Semantic Fluency	Secondary
**Blood-based markers**	
Cholesterol levels (total, HDL, LDL, triglycerides)	Secondary^1^
HbA1c levels, %	Secondary^1^
Creatinine-based eGFR levels	Secondary^1^
**Clinical measures**	
Height and weight (BMI)	Secondary^1^
Blood pressure (systolic and diastolic)	Secondary^1^
**Medical history and medication**	
Diabetes (and type)	Secondary^1^
Coronary heart disease	Secondary^1^
Kidney disease	Secondary^1^
Hypertension	Secondary^1^
Hypercholesterolemia	Secondary^1^
Depression	Secondary^1^
Hearing loss	Secondary^1^
Sleep disorders	Secondary^1^
Smoking (quantity, duration)	Secondary^1^
Alcohol intake (quantity, duration)	Secondary^1^
**Questionnaires**	
* Lifestyle*	
Mediterranean Diet Adherence Screener (MEDAS)	Secondary^1^
European Prospective Investigation into Cancer and Nutrition (EPIC) physical activity questionnaire	Secondary^1^
Cognitive and Leisure Activities Scale	Secondary^1^
Perceived Stress Scale	Secondary
Patient Health Questionnaire (PHQ)−9	Secondary^1^
Groningen Sleep Quality Scale (GSKS)	Secondary^1^
6-item Lubben social network Scale	Secondary^1^
De Jong Gierveld 6-item Scale	Secondary
* Daily functioning and psychological*	
Amsterdam-Instrumental Activities of Daily Living (ADL)-Questionnaire	Secondary
Health locus of Control Scale	Secondary
General Self-Efficacy scale	Secondary
Pearlin Mastery Scale	Secondary
* Knowledge*	
Knowledge on dementia risk questionnaire	Secondary
**Process evaluation**	
Mixed-method on implementation, context, mechanism of impact (questionnaires, interviews, focus-groups, data registration)	Secondary
**Cost-effectiveness**	
EuroQol-5D-5 L	Secondary
ICEpop CAPability measure for Older people (ICECAP-O)	Secondary
Medical Consumption Questionnaire (iMCQ)	Secondary
Productivity Costs Questionnaire (iPCQ)	Secondary

All measures were performed at baseline and 12 months

*Abbreviations*: *LIBRA2 *LIfestyle for BRAin health 2, *WAIS *Wechsler Adult Intelligence Scale, *TMT *Trail Making Test, *HDL *high-density lipoprotein, *LDL *low-density lipoprotein, *HbA1c* glycated hemoglobin, *eGFR *estimated Glomerular Filtration Rate, *BMI *body mass index, *MEDAS *Mediterranean Diet Adherence Screener, *EPIC *European Prospective Investigation into Cancer and Nutrition, *PHQ-9 *Patient Health Questionnaire-9, *GSKS *Groningen Sleep Quality Scale, *ADL *Activities of Daily Living, *ICECAP-O* ICEpop CAPability measure for Older people, *MCQ *Medical Consumption Questionnaire, *PCQ *Productivity Costs Questionnaire

^1^Primary outcome as part of LIBRA2, secondary outcome as assessed individually

### Primary outcome

The primary outcome is the 1-year change in participants’ modifiable dementia risk profile as measured by the LIBRA2 score (Fig. 2). LIBRA2 comprises of 15 modifiable dementia risk and protective factors identified through an umbrella review and expert consensus study: coronary heart disease, diabetes, hypercholesterolemia, hypertension, depression, obesity, smoking, high physical activity, chronic kidney disease, high alcohol intake, high cognitive activity, healthy diet, hearing impairment, sleep disturbances, and social participation [4, 22]. Each of these factors has an assigned weight based on the factor’s relative risk for dementia from meta-analyses as shown in Supplementary Table 1 [23]. Based on the presence or absence of risk or protective factors, these weights are summed to yield a total LIBRA2 score. Higher scores indicate an unhealthier lifestyle profile and a higher risk of dementia, with a total score ranging from − 6.1 to 25.7. LIBRA2 was constructed in 2024 and represents an update of the original LIBRA index, in which three risk- and protective factors were added (hearing impairment, sleep, social participation). The LIBRA index has been extensively validated to predict brain damage, cognitive decline, incident cognitive impairment and dementia in various population-based studies [28–30] and clinical studies in people with SCD or MCI [31, 32]. LIBRA2 is recently validated in the English Longitudinal Study of Ageing and the Maastricht Ageing Study, showing increased overall performance compared to LIBRA [23]. Yet, validation in clinical samples remains to be established. It has also been included as outcome measures in other multidomain intervention studies targeting the general population [14, 16, 33, 34] and the ongoing 2-year multidomain FINGER-NL trial [35], and has been recommended as a surrogate outcome measure in prevention studies by the World Health Organization’s brain health group [36] and the World Wide FINGER group [20]. Table 2 describes the measurement of each LIBRA2 factor in this study, including the cut-offs that will be applied to assess the presence of the risk factors.

**Fig. 2 Fig2:**
[figure not shown]
Risk and protective factors captured by the Lifestyle for Brain Health score (LIBRA2). Percentages indicate the weight of the risk factors involved as calculated by LIBRA2

**Table 2 Tab2:** Assessment of the presence of LIBRA2 risk factors

LIBRA2 factor	Assessment
Obesity	BMI ≥ 25, for persons aged 65 years and older BMI ≥ 28 (risk defined by overweight rather than obesity cut-offs)
Depression	Self-report on depression diagnosis OR PHQ-9 ≥ 10
Hypercholesterolemia	Self-report on hypercholesterolemia diagnosis OR usage of statins OR Total Cholesterol ≥ 5 mmol/L OR LDL cholesterol ≥ 3.5 mmol/L
Heart disease	Self-report on coronary heart disease diagnosis OR using drugs for heart disease (e.g. anticoagulants)
Hypertension	Self-report of hypertension diagnosis OR usage of antihypertensives OR mean diastolic blood pressure ≥ 90 OR mean systolic blood pressure ≥ 140
Diabetes	Self-report on diabetes type 2 diagnosis OR usage of glucose-lowering drugs (e.g. insulin, metformin) OR HbA1c ≥ 48 mmol/mol
Kidney disease	Self-report of chronic kidney disease diagnosis OR eGFR measure of < 60
Hearing impairment	Self-report of hearing impairment OR hearing aids
Sleep	Low sleep quality indicated by the GSKS score ≥ 5
Physical activity	EPIC physical activity questionnaire in inactive or moderately inactive category following the Cambridge physical activity index
Cognitive activity	Low cognitive activity indicated by the Cognitive and Leisure Activities Scale ≤ 30
Social participation	Low social engagement indicated by the 6-item Lubben social network Scale ≤ 14
Smoking	Self-report of current smoking
Alcohol	Self-report quantity of > 7 glasses per week
Healthy diet	No adherence to healthy diet indicated by the MEDAS score *<* 8

*Abbreviations*: *BMI *body mass index, *PHQ-9 *Patient Health Questionnaire-9, *LDL *low-density lipoprotein, *HbA1c *glycated hemoglobin, *eGFR* estimated Glomerular Filtration Rate, *GSKS *Groningen Sleep Quality Scale, *EPIC *European Prospective Investigation into Cancer and Nutrition, *MEDAS *Mediterranean Diet Adherence Screener

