### Secondary outcomes

#### Individual LIBRA2 factors

Measures of all individual factors of the LIBRA2 are included as separate secondary outcomes. These include questionnaires on mediterranean diet (Mediterranean Diet Adherence Screener; MEDAS) [37], physical activity (European Prospective Investigation into Cancer and Nutrition; EPIC) [38], cognitive activity (Cognitive and Leisure Activities Scale) [39], depression (PHQ-9) [40] and stress (Perceived Stress Scale) [41], sleep quality (GSKS) [42], social participation (Lubben social network scale) [43] and loneliness (De Jong Gierveld 6-item Scale) [44]. Questionnaires have been validated and used in previous Dutch studies [35, 45]. Participants complete these questionnaires online at home (via Castor EDC). If this is not feasible, participants are provided the opportunity to complete the questionnaires on paper. Smoking and alcohol use (including duration and quantity) and diagnosis of health conditions (hypertension, hypercholesterolemia, coronary heart disease, diabetes, kidney disease, depression, sleep disorders) are assessed through self-report.

Objective measures to define obesity and hypertension include height, weight, and blood pressure (average of three measures while sitting). Lab measures are used to objectively define hypercholesterolemia (through total cholesterol, LDL cholesterol, HDL cholesterol, and triglyceride levels), diabetes (through HbA1c levels), and kidney disease (through creatinine/eGFR levels). These are determined in the blood by standard local protocols (5 ml serum for HbA1c, 4 ml heparin for creatinine and lipids). The presence of health conditions is operationalized through either the presence of a self-reported diagnosis or abnormal values of objective measures, using the same cut-offs as used for calculating LIBRA2 (Table 2).

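### Table 2 scores the coronary heart disease factor of LIBRA2 on any drug for heart disease, which is wider than the condition that carries the weight

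*Protocol article*

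**What the plan says.** The Primary outcome section defines the endpoint: "The primary outcome is the 1-year change in participants’ modifiable dementia risk profile as measured by the LIBRA2 score". Among the 15 factors it lists are "coronary heart disease, diabetes, hypercholesterolemia, hypertension, depression, obesity, smoking, high physical activity, chronic kidney disease". On weighting it states: "Each of these factors has an assigned weight based on the factor’s relative risk for dementia from meta-analyses". On construction: "Based on the presence or absence of risk or protective factors, these weights are summed to yield a total LIBRA2 score".

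Table 2, which that section presents as the measurement of each factor in this study, labels the row simply as heart disease and scores it on "Self-report on coronary heart disease diagnosis OR using drugs for heart disease (e.g. anticoagulants"). Table 1 lists the item as coronary heart disease, under medical history and medication.

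The section Individual LIBRA2 factors puts coronary heart disease among the diagnoses obtained by self-report. It then says: "The presence of health conditions is operationalized through either the presence of a self-reported diagnosis or abnormal values of objective measures". That sentence has no medication route, although it refers to Table 2 for the cut-offs.

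**The concern.** The weight belongs to coronary heart disease and reflects that condition's own relative risk. The rule that triggers the weight is joined by OR to a drug criterion that does not mention coronary disease, and no check of the indication is stated. The one example given, anticoagulants, is not specific to coronary disease. A participant on such a drug for atrial fibrillation meets the criterion as written.

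The other drug routes in Table 2 fit their factor: statins for hypercholesterolemia, antihypertensives for hypertension, glucose-lowering drugs for diabetes. Only the heart row uses a drug group broader than the factor.

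What is at stake is a measurement error in one component of the primary score. Two analysts could also score the individual heart factor differently, depending on whether they follow Table 2 or the text on individual factors. The cost-effectiveness model simulates dementia onset from LIBRA2 risk factors, so the error can enter there as well.

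**Working it through.** **1. The definitions side by side**

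| Place | Condition named | Route to a positive score |
|---|---|---|
| Primary outcome, text | Coronary heart disease | Presence or absence, coronary weight |
| Table 1 | Coronary heart disease | Medical history and medication |
| Table 2 | Heart disease | Self-reported coronary diagnosis, or a drug for heart disease |
| Individual LIBRA2 factors, text | Coronary heart disease | Self-reported diagnosis; no drug route stated and no objective measure named |

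The condition and the role of medication do not agree across these places.

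**2. The plan's own figures**

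The Sample size section equates 1 LIBRA2 point with d = 0.35, so SD = 1/0.35 = 2.857. By the normal approximation, n = 2(1.960 + 0.842)² × 2.857² / 1² = 128.1, that is 129 per group. The t-test version gives 129.1, that is 130. The stated 133 is slightly larger and has 81.2% power by t-test. Dropout: 133/0.9 = 147.8, rounded up to 148, and 2 × 148 = 296. The sample size is therefore reproduced closely enough to serve as the yardstick.

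**3. Inputs that must be assumed**

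- Coronary weight w: 0.5 to 3 points. The weights are in Supplementary Table 1, which is not at hand. For orientation, the article gives the total score as "with a total score ranging from − 6.1 to 25.7", a span of 31.8, or 31.8/15 = 2.12 per factor on average.
- Share m wrongly scored present: 5% to 15%, that is 15 to 45 of 300.
- Participants who start or stop such a drug within the year: 1% to 3%, that is 3 to 9 of 300.

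**4. Effect on score level and spread**

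Each affected participant carries w too much, so the mean rises by w × m. If the error is independent of the true score, SD = √(2.857² + w² m(1 − m)). Required n and power below use the normal approximation for a 1-point difference in follow-up scores.

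| w | m | Mean shift | SD | n per group | Power at 133 |
|---|---|---|---|---|---|
| 0.5 | 5% | 0.025 | 2.859 | 129 | 81.4% |
| 1 | 10% | 0.10 | 2.873 | 130 | 81.0% |
| 2 | 10% | 0.20 | 2.919 | 134 | 79.8% |
| 3 | 15% | 0.45 | 3.051 | 147 | 76.2% |

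**5. Effect on the 1-year change**

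Write e = 1 if the participant is wrongly scored present at a visit. Observed change = true change + w(e at 12 months − e at baseline). Where e is the same at both visits, the error drops out. The bias in the arm difference is w times the net between-arm difference in starts minus stops. With a net difference of 1 to 3 percentage points, this runs from 0.5 × 0.01 = 0.005 to 3 × 0.03 = 0.09 points. If starts and stops are unrelated to allocation, the expected value is zero and only a little noise remains.

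**The case against.** The strongest reply is that the rule has a qualifier: the drug must be used for heart disease. That stands, and it limits the point in several ways.

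- A reader might infer that an anticoagulant for venous thrombosis also scores, or that an antihypertensive taken only for hypertension scores twice. On the plain wording neither is a drug for heart disease, and hypertension has its own row. The qualifier does not exclude atrial fibrillation or other non-coronary heart disease, and that is the part that survives.
- A reader might infer that the treatment effect is biased. The article gives no reason to expect starts and stops to differ by arm, and step 5 gives a small figure even if they do.
- A reader might infer that coaching is misdirected. The coach works from the profile ("The coach discusses the individual lifestyle risk profile (based on baseline LIBRA2 measures, see below"), and a wrong flag could appear in the binder. But advice follows factors with room for improvement, vouchers cover activity, social, cognitive and diet domains, and heart disease is not an eligibility factor. Nothing ties the flag to a goal or voucher.
- A reader might infer that the individual coronary outcome is mislabelled. The text on individual factors points to self-report, so this holds only if that outcome is scored by Table 2.

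It can also be said that an article shortens row labels and leaves drug lists to a manual, and that the sentence on health conditions omits medication for every condition. That is fair for the label and the drug list. It does not explain why the stated criterion and its only example are broader than the factor.

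**Conclusion.** The point holds as a definition error in one component of the primary score. Followed as written, Table 2 gives the coronary weight to participants whose heart condition is not coronary, and the sections defining the factor do not agree.

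The effect on the primary comparison is small: 0.005 to 0.09 points against the 1-point target under the assumed ranges, with zero expected if drug changes are unrelated to allocation. The mean score level would be 0.025 to 0.45 points too high under the same kind of assumption. The power loss in step 4 applies to a comparison of follow-up scores, the basis of the sample size. The planned mixed model uses baseline as well, so a stable error matters less there.

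The main consequences are for score level, baseline description, the individual heart factor if it follows Table 2, and the risk-factor inputs to the cost-effectiveness model. Every size given here rests on assumed values for the coronary weight and for drug use without coronary disease. A claim that the coronary factor is badly distorted would need those figures.

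**What to change.** - In Table 2, name the row coronary heart disease. Score it on a self-reported coronary diagnosis, or on medication only when it is taken for coronary heart disease. Remove the anticoagulant example.
- In Individual LIBRA2 factors, state whether medication counts, and use the same rule for the individual secondary outcome as for LIBRA2.
- Apply the one rule at baseline and at 12 months, and rescore baseline records where the indication is recorded.

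This changes scoring only, not care or data collection, since medication is already assessed at both visits. The article does not say whether the indication is recorded; if it is not, it would need to be added at follow-up, and baseline records without it could be scored on self-report alone. The cost is some loss of sensitivity: participants with unreported coronary disease and no recorded indication may be missed.
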